# A study protocol of Older Person’s Exercise and Nutrition Study (OPEN) - a sit-to-stand activity combined with oral protein supplement – effects on physical function and independence: a cluster randomized clinical trial

**DOI:** 10.1186/s12877-018-0824-1

**Published:** 2018-06-07

**Keywords:** Interview, Mobility, Nursing home, Nursing staff, Nutrition, Older person, Oral nutritional supplement, Physical function, Quality of life, Sit-to-stand

## Abstract

**Background:**

Poor nutrition and age per see add to the development of sarcopenia, i.e. loss of muscle mass and strength, which contributes to increased risk of impaired activities of daily living (ADL) and reduced independence. Protein deficiency plays an important role in the development of sarcopenia. In order to increase the muscle mass protein intake should be combined with physical exercise. A daily physical activity, the sit-to-stand exercise, has been proven to decrease older persons’ dependence in ADL. Our study aims to evaluate the effects of the sit-to-stand exercise in combination with a protein-rich nutritional supplement, on physical function and independence in frail nursing home residents. The resident’s perceptions and experiences of the intervention and the staff’s experiences of supporting the resident to complete the intervention will also be explored.

**Methods:**

The study is a two-arm cluster-randomized controlled trial which will be performed in nursing homes at two municipalities in Sweden. We will recruit 120 residents, age 75 or older and able to stand up from a seated position. Residents (*n* = 60) randomized to the intervention group will perform the sit-to-stand exercise at four occasions daily and will be offered a protein-rich oral supplement, twice a day. The intervention period will last for 12 weeks and measures of physical function, nutritional status, quality of life and health economy will be performed at baseline and at 12-weeks follow-up. The primary outcome will be the number of chair rises performed in 30 s. The control group will receive standard care. Data will be analysed by intention-to-treat analysis and with mixed effect models. During the last part of the intervention period individual interviews with the residents, on the topic of feasibility with the OPEN concept will be held. Likewise, focus-group-interviews with staff will be performed.

**Discussion:**

The residents’ physical and mental health could be expected to improve. Even the work situation for staff could be positively affected. One innovative feature of the OPEN study is the simple intervention consisting of a basic daily activity that can be performed by several nursing home residents with the support of existing staff and available resources.

**Trial Registration:**

ClinicalTrials.gov Identifier: NCT02702037.

## Background

Active ageing is a concept introduced by World Health Organization in 2002 and defined as “*the process of optimizing opportunities for health, participation and security in order to enhance quality of life as people age”* [1]. Active ageing should be implemented for all older persons. For older residents living in nursing homes (NH), activities as meaningful leisure and participation, including physical activity, should be considered [2]. This is in line with the call for person-centered care where the focus is on the person’s expectations, resources, needs and abilities, and not on the symptoms and diseases. [3].

In spite of the knowledge of the health-related benefits of active aging and daily physical activity [2, 4], a majority of NH residents are inactive most of the time and with little social interaction [4–6]. This sedentary living is not necessarily due to medical conditions or decreased mobility function. The ward staff is often taking over the activities from the resident, in the meaning of being helpful, instead of letting the resident perform the activities, or part of activities, by themselves [7]. Mobility is identified by residents as a central importance to quality of life and well-being [8] and disability is one of the most consistent risk factors for depression in later life [9]. Inactivity and lack of social interaction can also lead to melancholy. Further, reduced activity and impaired mobility increases the risk of falls, pressure ulcers and incontinence [10, 11] all of which can lead to complications, hospitalization and reduced health-related quality of life [12]. Residents that are unable to move around independently, and even must rely on lifts for ambulation, often bears greater costs of care [13].

Aging causes loss of muscle mass and function which, along with poor nutrition contributes to increased risk of frailty. Sarcopenia, i.e., loss of muscle mass and muscle strength is probably the largest single cause of this scenario [14]. Sarcopenia often occurs in frail and sick older persons and leads to impaired ability to perform activities of daily living (ADL) such as walking, toileting, eating and socializing and thereby to increased dependence [12]. Protein deficiency seems to play an important role in the development of sarcopenia in older persons and for this reason the PROT-AGE study group as well as the New Nordic Recommendations recommend an increase in protein intake in older persons [15, 16]. In order to increase the muscle mass, the protein intake must be combined with physical exercise [17, 18].

It is possible to affect muscle strength with various forms of exercise, even in older NH residents. Progressive resistance training has been most studied [19]. High intensity group exercise program lead by physiotherapists has shown to improve balance control, strength and gait ability in frail older residents [20]. Similar to other studies [4], they investigated group training, distributed 3 times per week and on a relatively high level of intensity. However, there is scarce knowledge of the relation between the dose (frequency, duration, and intensity) of exercise in relation to the health outcomes. Frail older NH residents might benefit more by shorter exercise sessions several times a day rather than fewer and longer [21]. One functional and very essential exercise for older frail persons is standing up from a seated position and sitting down in a controlled manner - the sit-to-stand (STS) exercise. The ability to rise from a chair without help from others requires leg muscle strength and is fundamental for independent mobility. It is a simple activity, which as a physical exercise, does not require additional equipment and resources in the institutional setting. The exercise can be integrated with daily activities such as dressing, toileting or meals. The STS exercise has been studied in different settings with promising results [22–24]. A randomized-controlled trial study from Canada that evaluated the effects of STS exercise offered four times per day on seven days per week among older residents with dementia (mean age 88 years) living in long-term care facilities demonstrated less decline in mobility and functional outcomes in the intervention group compared with the control group [25].

In line with the above mentioned recommendations, a meta-analysis including 22 RCTs in both young and older subjects found that protein supplementation augments the adaptive response of skeletal muscle to resistance-type exercise training [17]. Protein supplementation improved physical performance and increased muscle mass gain during prolonged resistance-type exercise training in frail older people [18]. Moreover, a low protein intake in older persons in combination with low energy intake contributes to malnutrition and around 50% of older NH residents are assessed at risk of malnutrition [26]. For this reason, the OPEN-study aims to study the combination of exercise and protein supplementation on muscle mass and function.

Although there is evidence that STS exercise stabilizes older persons’ mobility, no studies are published exploring the older person’s experiences or perceptions of the STS exercise, neither on staff’s experiences on supporting older persons to complete the exercises. Interviews with older women with osteoporosis on their perceptions and experiences of physical training have revealed that personal preferences and individualization including support from health professionals was perceived as important [27]. Furthermore, there is a general lack of studies measuring the effectiveness of STS activities in this population. The novelty with the OPEN study is to evaluate the effects of the STS exercise during routine care, in combination with a protein-rich nutritional supplement, on functional status and independence in frail NH residents.

### Objectives

The main hypothesis of the OPEN study is that physical exercise performed as a daily routine along with a protein supplement, will result in improved physical function status and independence in everyday life activities and thereby enhance health-related quality of life in older persons living in nursing homes.

Specific aims of the study are:*Aim I:* To investigate the effects of the STS exercise combined with an oral protein-rich supplement on physical function and nutritional status, and health-related quality of life, and the frequency and incidence of falls, pressure ulcers and incontinence in older nursing home residents.*Aim II:* To estimate the cost effectiveness of the combination of the STS exercise and oral protein-rich supplement vs. the control group.*Aim III:* To describe the residents’ perceptions and experiences of daily being offered to conduct the STS exercise and to drink the nutritional supplement.*Aim VI:* To describe nursing home staff’s experiences of supporting the STS exercise and to offer the nutritional supplement to residents.

## Methods

### Trial design

This study protocol has been informed by the SPIRIT guidelines [28]. The study is a two-arm cluster-randomized controlled trial which will be performed in NH at two municipalities in the Stockholm area. There are in total 62 NH units (34 dementia care, 28 somatic care; approx. 571 beds). A cluster will be defined as a group of 1–3 NH units with in total approximately 15–38 persons depending on the size of a unit. The clusters will be randomized according to a computer based sample list into two groups; intervention group and control group. The cluster design is chosen to prevent spread of the STS exercise to the control groups. This study has been registered with the number protocol of ClinicalTrials.gov Identifier: NCT02702037. An overview of the study is presented in Fig. 1.

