### Sample size calculation

The sample size calculation for the number of participants is based on the effect size of the primary outcome measure in a pilot study performed and described in a study protocol by a Canadian research group that we collaborate with [24]: that is the number of sit-to-stands that the participant is able to complete in 30 s. An increase of 2 sit-to-stands completed in 30 s is suggested to be a meaningful change in the person’s mobility. Based on existing research [30, 43–45] the standard deviation of the 30-s sit-to-stand measure is 3.5 sit-to-stands. Based on the power calculation by Slaugther and colleagues [24], 49 participants in each group are needed to detect an increase in the number of sit-to-stands (power = 0.80; 2-tailed; α = 0.05). Assuming an attrition of 20% over the 12 weeks, we will recruit in total 120 participants (60 participants to each group).

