### Data analyses

All data will be entered into a database using SPSS (iBM). Quality controls will be made to check that the data are entered correctly. The baseline characteristics of the participants in the intervention and control groups will be compared using descriptive statistics. All analysis will be done by members of the research group and by an independent statistician respectively.

Data for primary and secondary outcome measures will be analysed using descriptive and comparative statistical analyses including multi-level statistics appropriate for the data measurement levels and data distributions. Data will be analysed according to intention-to-treat, i.e. participants who will drop out before completing the 12 weeks of follow up will be included in the data analysis. The model of data analysis needs to consider the effect of clustering. Thus, this study will use mixed effect models with the cluster treated as a random effect.

Combining the resource units with the cost price will allow the calculation of total costs of each group. The cost effectiveness calculation will use the EQ5D-5 L as outcome. Costs and effects will be examined based on the principle of cost-consequence analysis. This type of analysis lists all relevant costs and effects (consequences) in order to capture as much information as is feasible, in order to allow decision makers to choose the outcome of interest for inclusion in economic analyses [54].

The qualitative data consisting of tape-recorded interview-answers will be transcribed verbatim. The qualitative data sets will be analysed from a data-driven inductive approach. More specifically, the transcripts of the interviews will be read and analysed using a constant comparative method described by [29].

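### Cluster allocation is described without balancing by unit type, leaving a material but not expected risk of chance imbalance between dementia and somatic care

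*Protocol article*

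**What the plan says.** Trial design in the protocol article sets out the setting: "The study is a two-arm cluster-randomized controlled trial which will be performed in NH at two municipalities in the Stockholm area". It then describes the pool: "There are in total 62 NH units (34 dementia care, 28 somatic care; approx. 571 beds". Clusters are built from these units: "A cluster will be defined as a group of 1–3 NH units with in total approximately 15–38 persons depending on the size of a unit". Allocation is covered in one statement: "The clusters will be randomized according to a computer based sample list into two groups". The article mentions no strata, blocks, matching or constraint. It gives no number of clusters, and it does not say whether one cluster may hold both unit types.

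Data analyses gives the model class: "this study will use mixed effect models with the cluster treated as a random effect". No fixed covariate is listed and none is ruled out.

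Sample size calculation supplies the scale. The target is given as "An increase of 2 sit-to-stands completed in 30 s is suggested to be a meaningful change in the person’s mobility", and the spread as "the standard deviation of the 30-s sit-to-stand measure is 3.5 sit-to-stands".

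**The concern.** Unit type is a property of the unit, known before randomisation. The primary outcome is an instructed performance test, and the exercise relies on staff support, so dementia and somatic units could plausibly differ in outcome. The article reports the split between the two types but does not use it in the allocation it describes.

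When clusters are allocated from an unrestricted list, the arms can by chance receive different shares of dementia units. A cluster random effect carries between-cluster variation into the standard error. It does not move the point estimate back when a cluster-level factor is unevenly split in the trial actually run. At stake are a conditional shift in the single primary comparison, and precision that balanced allocation with a matching model term would keep. Allocation is fixed before the trial starts, so a later analysis plan can adjust for an imbalance but cannot prevent one.

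**Working it through.** **Inputs from the protocol article.** 62 units, 34 dementia and 28 somatic, about 571 beds; clusters of 1–3 units and about 15–38 persons (Trial design). Target 2 rises, SD 3.5, power 0.80, two-sided α 0.05, 49 per arm before attrition, 120 in total (Sample size calculation).

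**Assumptions.** Clusters are allocated 1:1. Single-type clusters carry equal weight. The dementia share of clusters is 34/62 = 54.8%, rounded to a whole number of clusters. The difference between unit types is taken as 1–2 rises; the documents give no figure.

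**The plan's own figure.** n = 2 × [3.5 × (1.960 + 0.842)/2]² = 48.07, which rounds up to the stated 49 per arm. The individual-level standard error of the arm difference is then 3.5 × √(2/49) = 0.71 rises. It is used below only as a yardstick.

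**How many clusters.** By beds, the whole pool gives 571/38 = 15 to 571/15 = 38. By units, at most three per cluster gives 62/3, so 21 or more. Counts below 21 therefore mean that part of the pool is not used. That is possible, because enrolment stops at 60 per arm.

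**Single-type clusters, exact hypergeometric.** With K clusters, D of them dementia and K/2 per arm, let x be the dementia clusters in one arm. Then P(x) = C(D,x)·C(K−D, K/2−x)/C(K, K/2), and the gap is |x − (D−x)|/(K/2).

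- K = 16, D = 9: a 5:4 split is a gap of 12.5 points and the next is 37.5. P(gap ≥ 30) = 1 − 2·126·35/12870 = 0.31.
- K = 20, D = 11: a 6:5 split is 10 points and the next is exactly 30. P(gap ≥ 30) = 1 − 2·462·126/184756 = 0.37.

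| Clusters | P(gap ≥ 30 points) | SD of gap |
|---|---|---|
| 8 | 49% | 0.38 |
| 15 | 32% | 0.27 |
| 16 | 32% | 0.26 |
| 20 | 37% | 0.23 |
| 24 | 10% | 0.21 |
| 30 | 7% | 0.19 |
| 38 | 5% | 0.16 |

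(For odd K the arms differ by one cluster.)

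The probabilities jump because only certain gaps can occur, so they should not be interpolated. At K = 18 (D = 10) the result is 1 − (252·70 + 2·210·56)/48620 = 15%. At K = 26 (D = 14) it is 1 − (3432·924 + 2·3003·792)/10400600 = 24%. The SD of the gap, 2√[p(1−p)/(K−1)] with p = D/K for equal arms, falls smoothly and is the steadier guide.

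The threshold also matters. On a 50-point gap, 16 clusters gives 2 × (252 + 9)/12870 = 4%.

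**Mixed clusters, simulation.** 20,000 runs per cluster count; clusters of 1–3 units drawn at random from the 34 and 28; runs needing more than 62 units dropped. P(gap ≥ 30 points): 25% at 8 clusters, 11% at 15, 6% at 20, 2% at 30.

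**Effect on the estimate.** Shift = gap × difference between unit types. A 30-point gap gives 0.30 × 1 = 0.3 to 0.30 × 2 = 0.6 rises. That is 15–30% of the 2-rise target, or 0.3/0.71 = 0.4 to 0.6/0.71 = 0.85 of the individual-level standard error.

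**Effect on precision.** Left out of the model, the type difference contributes (34/62)(28/62) × 1² = 0.25 to (34/62)(28/62) × 2² = 0.99 to the variance, about 2–8% of 3.5² = 12.25. It does so however the clusters happen to fall.

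**The case against.** The strongest reply is that much of this rests on what a condensed article does not say. A computer-based list may itself have been blocked or stratified, and the design figure is not available. Covariates are commonly left to the analysis plan, which is not shown, and the article excludes none. Baseline chair rises and the MMSE are both measured, so adjustment stays possible. Residents who cannot follow instructions are excluded and all participants must be able to stand, which narrows any difference between unit types. Randomisation is also unbiased on average.

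Most of this stands, and it rules out several stronger readings that a reader might infer:

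- That there are few clusters. No count is given. Eight clusters would need 120/8 = 15 participants from each group of 15–38 persons, that is 39–100% of every cluster. That sits badly with the exclusions and with the prolonged recruitment the Discussion expects.
- That a large imbalance is likely. None of the tabulated probabilities reaches one half.
- That clusters mix the two types. The text does not say so, and mixing would reduce the imbalance.
- That the model leaves unit type out. It is not stated either way.
- That imbalance inflates between-cluster variance. That variance comes from the difference between unit types, however they are allocated.

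What the reply does not remove is that the article describes how clusters are allocated, reports the unit-type split alongside, and does not connect the two.

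**Conclusion.** The point holds as a design weakness of moderate weight. As described, allocation does nothing to balance unit type, and the one model term named would not correct an imbalance in the arm estimate. Over the cluster counts tabulated from 15 to 38, the chance of a gap of 30 points or more runs from 37% down to 5% with single-type clusters, and from 11% at 15 to 2% at 30 with mixed ones. Such a gap would shift the unadjusted difference by 0.3–0.6 rises if unit types differ by 1–2 rises.

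The conclusion depends on the unstated number and make-up of clusters, on equal cluster weights, and on that assumed difference. The documents do not support calling this a systematic bias or the expected result. It is a material risk of conditional imbalance and some lost precision, and both are cheap to reduce.

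**What to change.** Before allocation: state the number of clusters, form each within one unit type where possible, and stratify or constrain the cluster randomisation by unit type, and by municipality if numbers allow. The first step needs the second: single-type clusters without stratification carry the larger gaps shown above. With both, the gap is held to about one cluster; for 20 clusters with 11 dementia, 6 against 5 is 10 points. Where a cluster has to combine types, constrain the allocation on its share of dementia units.

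In the primary mixed model, include unit type as a fixed effect beside the cluster random effect. If allocation is already done, add the model term only.

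The cost is a revised allocation list and one or two cluster-level degrees of freedom. Single-type clusters may also place neighbouring units in different arms, which has to be weighed against the article's aim of keeping the exercise from spreading to controls.

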**Fig. 1 Fig1:**
[figure not shown]
Design of the OPEN study

### Ethics

The study has been approved by the Regional Ethical Review Board in Stockholm, D no. 2013/1659–31/2, 2015/1994–32 and 2016/1223–32. Major changes in the study protocol will be communicated to EPN for approval.

### Participants

Residents aged ≥75 years living in NH’s in the two municipalities will be invited to participate. Screening of all residents in the participating NH according to inclusion and exclusion criteria will be conducted by ward nurses and physiotherapists in cooperation with research staff. Eligible subjects will then be approached in person by the research staff for verbal informed consent. Information about the study will be given both in oral and written form.When needed, the research staff will read the written information loud to the older person.

#### Inclusion criteria

Able to rise from a seated position to standing.

#### Exclusion criteria

Persons with a Body Mass Index (BMI) > 30, treated with protein-rich oral supplement, suffering from severe dysphagia, tube fed, bedridden, severe kidney disease, at a terminal stage of life, lack of informed consent will be excluded. Resident who by the responsible nurse is assessed as not eligible to participate due to psychological or cognitive reasons will also be excluded. Psychological reasons is defined as anxiety and/or risk for increased behavioral problems due to something new added to the person’s daily life. Cognitive reasons is defined as not be able to follow instructions.

Among the older persons who have accepted participating in the intervention group, approximately 20 persons will be invited to participate in individual interviews. This is a number estimated to secure data saturation, which is strived for in Grounded theory methodology [29].

Staff, who will support the residents to complete the intervention, will be invited to participate in the qualitative part of the study. Staff will be recruited for interviews by convenience sampling, although with the criteria that they had experience of having supported residents with the intervention (STS and nutritional supplement).

